#### Intervention

Both treatment arms will include 18 sessions spread over a 14-week period, including 17 one-on-one sessions and 1 asynchronous session, where online material will be provided. All treatment sessions will have a duration of approximately 30 minutes and will take place at the cabinet of the respective therapists in Switzerland or in Belgium. If illness or vacation cause absences, participants and therapists are requested to catch up the missed sessions within the 14-weeks’ timeframe if possible. Final number of attended sessions will be recorded. Both treatment arms are organized equally: all participants will receive 3 sessions of PNE in the first 2 weeks, following 15 sessions of CTET (including integration of BWRP for the experimental group) in the remaining 12 weeks. The BWRP intervention will include a lifestyle approach, implying grading daily physical activity and exercise levels alongside of a change in diet to reduce weight. The structure of the sessions and the detailed content of the interventions can be found in Suppl. Material 2 and 3. After the post-intervention measurement, participants will be allowed to receive concomitant care (eg, physical therapy, nutritionist counseling, medication change), which will be monitored with the Medical Consumption Questionnaire during the follow-up period.^38^ Every 3 months, participants will receive and email invitation to complete the follow-up questionnaires via REDCap software (Vanderbilt University, Tennessee, USA) and to fill out a food diary at the 3-month (T2) and 6-month (T3) follow-up (see Table 2). To ensure data completeness, automated reminders will be set up through REDCap, and assessors will contact participants if data remains missing after a reasonable period. After the last follow-up assessment at 12 months (T5) and therefore completion of the study, participants will receive a total remuneration of €120 as travel reimbursement.

**Table 2 TB2:** Overview of the Time Schedule of All Assessments*^a^*

**Timepoint**	**Study Period**					
	**Baseline**	**Post-Intervention**	**Follow-Up**			
	**T0**	**T1**	**T2**	**T3**	**T4**	**T5**

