**Additional Outcomes**						
Therapy adherence		X				
Blinding—group allocation guess						X

^a^
Abbreviations: BMI = body Mass Index; BPI = Brief Pain Inventory; CNLBP = Chronic Non-specific Low Back Pain; EQ-5D-5L = EuroQol 5D-5L questionnaire; FABQ = Fear avoidance belief questionnaire; HC = hip circumference; iMCQ = Medical Consumption Questionnaire; iPCQ = Productivity Cost Questionnaire; PSQI = Pittsburgh Sleep Quality Index; T0 = baseline, 1 week before therapy starts; T1 = post-intervention measurement, 1 week after the 14-week trial; T2 = 3 month follow-up (online); T3 = 6 month follow-up (online); T4 = 9 month follow-up (online), T5 = 12 month follow-up (onsite); TSK = Tampa Scale of Kinesiophobia, WC = waist circumference; WHR = waist-to-hip ratio.

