#### Therapy Adherence, Adverse Events, and Discontinuation of the Trial

Therapists will be instructed to document the course of treatment as required by their workplace guidelines. After a participant completes the 14-week therapy period, the therapist will be asked to complete a questionnaire on therapy adherence, compliance, and any adverse events (see Suppl. Material 5). No serious adverse events are expected, and the trial is rated as low-risk category by the ethical committee. Nevertheless, in case of an adverse event, physical therapists will be advised to inform the research team immediately. Furthermore, discontinuation of the trial is considered unlikely. However, if a female participant becomes pregnant or a severe adverse event occurs, participation will be discontinued. In both countries, the principal investigators must inform the respective ethics committee about any adverse events as quickly as possible or within a timeframe of 7 days. Additionally, an annual report on safety, adverse events, and the general progression of the clinical trial will be submitted to the respective ethics committee.

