### Outcome Assessment and Data Collection

#### Primary Outcomes

Pain intensity will be measured using the Brief Pain Inventory (BPI) item: “Please rate your pain by circling the number that best describes your pain of the last 24 hours on average (0-10)” will serve as primary outcome.^42^ The primary endpoint is the between-group change in pain intensity from baseline to 12 months follow-up. The BPI is widely used to assess clinical pain and recommended for effectiveness trials in chronic pain^43^ and its reliability and validity has been established.^44^^,^^45^ A reduction of 30% in average pain intensity is considered clinically relevant.^43^ The BPI will be collected online using REDCap at baseline (T0), directly after the intervention (T1, immediate effects), and at 3-months (T2), 6-months (T3), and 12-months (T5) follow-up to capture short-, mid-, and long-term effects, respectively.

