	Rest activity cycles	Fitbit Sense (wrist-worn activity monitor)	To capture continuous rest/activity cycles an accelerometry (Fitbit Sense 1 or 2, Fitbit International Limited, Dublin 2, Ireland) is used. This wrist-worn package will be installed 1 week prior to the treatment, will continue throughout the 14 weeks treatment, and will end the day of the follow-up body composition measurement (T1). Participants are instructed to wear the device constantly (day and night) and to synchronize the watch with the app once a day to ensure data storage. At T5, the last follow-up measurement, the Fitbit is handed out again and the participants are instructed to wear the accelerometer for 1 additional week.
	Sleep quality	Pittsburgh Sleep Quality Index (PSQI), Fitbit	The PSQI is a widely used tool to assess sleep quality.^63^^,^^64^ The PSQI is assessed using the REDCap software.
	Sleep quantity	Fitbit Sense	Sleep quantity and quality will be monitored using the Fitbit watch, including sleep schedules, time spent in bed, sleep duration, wake duration, and number of awakenings. While these devices are not recommended for diagnosing sleep disorders, they are suitable for monitoring sleep–wake behavior over extended periods.
	Continuous physical activity	Fitbit Sense	Continuous physical activity and rest/activity cycles are measured with an activity monitor (Fitbit Sense 1 or 2). Data analysis occurs through Fitabase software. Next to physical activity, sedentary behavior will be investigated with the accelerometer data.
Costs			
	Medical consumption	Medical Consumption Questionnaire (MCQ)	Medical consumption (including co-interventions) will be recorded using the Medical Consumption Questionnaire, which is a generic instrument for measuring patients’ total (in-)direct medical consumption.^38^ The MCQ is assessed using the REDCap software.
	Indirect health costs	Productivity Cost Questionnaire (PCQ)	The Productivity Cost Questionnaire will be used to obtain data regarding the indirect costs (eg, costs due to absenteeism or presenteeism).^65^ Costs will be reported in non-aggregated form and will be calculated as “units consumed × unit cost.” Unit costs will be extracted from country specific databases for health care services and drugs. All costs will be expressed in 2026 Belgium euro and for Swiss data also in 2026 Swiss Francs. Intangible costs (eg, pain, stigma) will be omitted. The PCQ is assessed using the REDCap software.
Quality of life			

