	Quality of life	EuroQol EQ-5D-5L questionnaire	The EuroQol EQ-5D-5L questionnaire is used to assess quality of life and health profiles, which will be transformed to utilities using Belgium, UK, and German tariffs.^66^^,^^67^ Health utilities are then used to calculate quality adjusted life years for the cost-utility analysis. The EQ-5D-5L is assessed using the REDCap software.

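### Pregnancy or a severe adverse event ends "participation" and not only study therapy, so on a plain reading the 12-month pain score is lost although it could still be collected online (minor)

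*Protocol article*

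**What the plan says.** The rule stands in the section on therapy adherence, adverse events and discontinuation: "if a female participant becomes pregnant or a severe adverse event occurs, participation will be discontinued". The sentence before it says that "discontinuation of the trial is considered unlikely", and the same section expects no serious adverse events.

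The Intervention section places the end of the study at the last follow-up: "After the last follow-up assessment at 12 months (T5) and therefore completion of the study". The Primary Outcomes section defines the endpoint: "The primary endpoint is the between-group change in pain intensity from baseline to 12 months follow-up". It also has the pain item collected through REDCap at baseline, T1, T2, T3 and T5. Table 3 gives the same mode for medical consumption ("The MCQ is assessed using the REDCap software") and for quality of life ("The EQ-5D-5L is assessed using the REDCap software"), and likewise for productivity costs.

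The Statistical Analysis Plan section specifies an intention-to-treat analysis with a multilevel mixed model, and a health economic evaluation over 66 weeks. Nothing in the article says that a participant discontinued under the rule continues to receive questionnaires.

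**The concern.** Two decisions are joined in one word. Stopping a weight-loss and exercise programme in pregnancy or after a severe adverse event has an evident safety reason. Stopping a questionnaire does not. If the rule is applied as written, the trial gives up data that it could still obtain without a visit, and the 12-month pain score is always among them.

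The loss is also selective. It is triggered by a health event after randomisation that may bear on pain or on treatment. The 25% drop-out allowance may cover such cases in number, but it protects sample size and does not protect against selective loss. An analysis plan written later cannot restore scores that were never collected.

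**Working it through.** **1. What "participation" covers.** Three points favour leaving the study altogether. The rule does not say therapy, although the same section refers to the 14-week therapy period when it means that. The preceding sentence speaks of discontinuing the trial. The Intervention section puts completion at T5, so the follow-up year belongs to the study. One point favours therapy only: the footnote to Table 2 reads "T1 = post-intervention measurement, 1 week after the 14-week trial", so the authors sometimes use "trial" for the therapy period. Leaving the study is the plainer reading. Therapy only is possible but nowhere stated.

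**2. What is lost per affected participant on the plain reading.** Table 2 schedules the BPI after baseline at T1, T2, T3 and T5 (4 scores). It schedules the EQ-5D-5L and the two cost questionnaires at T1 to T5 (5 collections). Counting those due after the event:

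| Event falls | BPI lost (of 4) | EQ-5D-5L and cost questionnaires lost (of 5) |
|---|---|---|
| before T1 | 4 | 5 |
| T1 to T2 | 3 | 4 |
| T2 to T3 | 2 | 3 |
| T3 to T4 | 1 | 2 |
| T4 to T5 | 1 | 1 |

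The T5 score is lost in every row. Scores before the event remain in the mixed model.

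**3. How many participants.** The article gives no event rate. Assuming 1% to 5%: 252 × 0.01 = 2.5 and 252 × 0.05 = 12.6, so about 3 to 13 participants.

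**4. Effect on power and precision.** The planned size can be reproduced with a repeated-measures group-by-time test. Inputs from the article are partial η² = 0.02, 2 groups, 5 BPI time points, alpha .05, 95% power and 25% drop-out. Correlation 0.5 and sphericity are assumptions.

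- f² = 0.02/0.98 = 0.0204
- λ = f² × N × m/(1 − ρ) = 0.0204 × 94 × 5/0.5 = 19.2, which gives power 0.954 at N = 94
- 94/0.75 = 125.3, rounded up to 126 per country; 2 × 126 = 252, as planned

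If the losses came entirely on top of the 25% allowance, per-country power would be 0.952 (1%, N = 93.06) or 0.943 (5%, N = 89.3). Pooled power would stay above 0.999. These figures belong to the reconstructed group-by-time test, not to the 12-month contrast alone. For that contrast, losing a further 5% of the T5 scores raises the standard error by a factor of about 1/√0.95 = 1.026.

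**5. Possible shift in the 12-month contrast.** Shift = (excess discontinuations in one arm/126) × (departure of the unobserved pain from what the model predicts). There are 2 × 63 = 126 per arm. Both the excess (0 to 4) and the departure (1 to 3 points) are assumptions.

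- equal numbers and equal departure in both arms: 0
- 1/126 × 1 = 0.008
- 4/126 × 2 = 0.063
- 4/126 × 3 = 0.095

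The range is 0 to about 0.10 points on the 0–10 scale.

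**The case against.** The strongest reply is that this turns on one word in a condensed article. The section heading begins with therapy adherence, the surrounding sentences concern therapists' records and reports, and the full protocol or consent form may already keep these participants in follow-up. That stands as a reason for caution. It does not remove the point, because the article states an operative rule and does not merely leave a detail open.

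For pregnancy, stopping can also be defended. Pregnancy and a birth in the preceding year are exclusion criteria, pregnancy changes body weight, and later pain scores would partly measure pregnancy. This is partly a choice of what to estimate. But scores that have been collected can be set aside in a sensitivity analysis, while uncollected scores leave no choice.

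For severe adverse events, the only reporting route described is the treating therapist, with a questionnaire at the end of the 14 weeks. The article shows no route by which such an event in the follow-up year would trigger the rule. That stands, and it means the later rows of the table apply mainly to pregnancy.

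Finally, the mixed model accommodates missing values, and the number of and reasons for drop-out are compared between arms. These steps use the earlier scores and describe the loss, but they do not recover the 12-month score.

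**Conclusion.** A minor point and a cheap improvement. On the plain reading the rule costs each affected participant the 12-month pain score and any other online outcome still due, with no safety gain. The overall effect is probably very small: under the assumptions shown, a per-country power change of about one percentage point or less and a contrast shift of at most about 0.10 points.

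A reader might infer more than the article supports, in four ways:

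- **That follow-up certainly stops.** The therapy-only reading remains open.
- **That intention-to-treat is contradicted.** Scores before the event are still analysed as randomised. The principle is weakened by avoidable loss, not broken.
- **That the comparison is biased.** No event rate and no difference between arms is given, so bias is possible but not shown.
- **That an average loss per participant, or the power of the planned missingness check to detect the loss, can be quoted.** Either figure would need event times or event counts that the article does not give. A spread of events over the whole 66 weeks also fits poorly with the therapist-based reporting of adverse events.

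**What to change.** State that pregnancy or a severe adverse event stops study therapy only, and that the online questionnaires in Table 2, including the BPI, continue through T5 unless the participant withdraws consent. Omit on-site body measurements where they do not apply. Analyse as randomised, and add a sensitivity analysis that excludes scores recorded after pregnancy. If therapy only was always meant, one clarifying sentence is enough.

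The cost is a short amendment and information-sheet wording in both countries; the Ethics section names three approving committees. The 79 participants included when the article was written may need re-information. At that date 252 − 79 = 173 (69%) were still to enter. No new visit, instrument or change in sample size is needed. The downside is that a few scores will partly reflect the event itself; the sensitivity analysis shows this for pregnancy but not for severe adverse events.

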#### Treatment Fidelity

To verify treatment fidelity, therapy sessions will be audio-recorded (only after written consent of the participant) and scored according to pre-defined fidelity criteria (see Suppl. Material 6). These fidelity criteria were developed by the study consortium based on international guidelines and the Cognitive Therapy Adherence and Competence Scale.^39–41^ With this template, the quality of treatment delivery and the therapist’s adherence and competence in delivering the treatment will be scored. Furthermore, the fidelity checklist will be used during training discussions to establish therapists’ readiness, such as their ability to design and implement a gradual exercise program for a hypothetical patient with CNLBP. Moreover, these fidelity criteria will be used during the yearly refresher course for the therapists. In addition, standardized training of therapists based on the treatment manuals will be performed in both treatment arms. Details on the treatment manuals for both treatment arms and the therapists’ training can be found in Supplementary Materials 2–4.

### Outcome Assessment and Data Collection

#### Primary Outcomes

Pain intensity will be measured using the Brief Pain Inventory (BPI) item: “Please rate your pain by circling the number that best describes your pain of the last 24 hours on average (0-10)” will serve as primary outcome.^42^ The primary endpoint is the between-group change in pain intensity from baseline to 12 months follow-up. The BPI is widely used to assess clinical pain and recommended for effectiveness trials in chronic pain^43^ and its reliability and validity has been established.^44^^,^^45^ A reduction of 30% in average pain intensity is considered clinically relevant.^43^ The BPI will be collected online using REDCap at baseline (T0), directly after the intervention (T1, immediate effects), and at 3-months (T2), 6-months (T3), and 12-months (T5) follow-up to capture short-, mid-, and long-term effects, respectively.

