**Primary Outcome**						
**Pain intensity (BPI)**	X	X	X	X		X

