#### Statistical Analysis Plan

Prior to the analyses, visual inspection for assessing data plausibility will be performed, while the normality assumption will be checked using Q-Q-plots**.** Missing values will be checked for randomness by performing a logistic regression analysis, modeling the probability of missingness against baseline characteristics. If no significant associations are found, missingness will be assumed to be at random**.** Independent samples *t*-tests (for continuous variables) and chi-square tests (for categorical variables) will be performed at baseline to check whether the randomization was successful. If not, variables for which this was not the case will be included as confounders in the main analyses after the direction of the relationship was established using directed acyclic graphs (DAGs).^69^ Drop-out analysis will be performed using independent samples *t*-tests and chi-square tests on the baseline data, while the amount of and reasons for drop-out (participants are asked to give their reasons of withdrawal) will be compared between the experimental and control condition. This procedure will allow us to check whether differential drop-out (and thus attrition bias) is present. Again, variables subject to selection bias will be included as confounders (when identified as such by the DAGs) in the main analyses. General(ized) linear mixed modelling will be performed in R (RStudio version 1.1.383) to evaluate and compare (long-term) therapy effects between the experimental and control intervention. Both the distribution of the outcome measure and residual distributions will be checked for normality using Q-Q-plots. To account for clustering effects (ie, participants will be measured repeatedly, clustered within different hospitals or therapeutic settings), a multilevel model will be constructed, including three levels: (1) repeated measures, (2) clustered within the individual, and (3) clustered within a hospital or other therapeutic setting. This technique is particularly well fitted to analyze repeated measures over time in a hierarchical structure including missing values.^70^ To minimize issues related to multiple testing, contrast testing within the generalized linear mixed model framework will be applied. A priori defined contrasts between the groups will be tested using the R package “multcomp” and the function “glht.” Statistically significant differences will be defined at alpha level .05, and the effect size as well as clinically significant differences will be determined. In addition, numbers needed to treat will be calculated, after transforming the outcome to a binary variable, in analogy with previous research.^71^ Analyses will be performed based on the intention-to-treat principle. Afterward, per protocol analyses will be performed (as a form of sensitivity analysis) to evaluate the effect of therapy adherence and compliance.

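### The primary endpoint is change in pain from baseline, but no unconditional adjustment for baseline pain is written; if baseline is an unconstrained repeated outcome, precision is given away at 12 months

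*Protocol article*

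**What the plan says.** Under Primary Outcomes, the article takes the single average-pain item of the Brief Pain Inventory (BPI, 0 to 10) and states: "The primary endpoint is the between-group change in pain intensity from baseline to 12 months follow-up". The item is collected at T0, directly after the intervention (T1), and "at 3-months (T2), 6-months (T3), and 12-months (T5) follow-up to capture short-, mid-, and long-term effects, respectively". Table 2 marks the same five occasions.

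Under Statistical Analysis Plan, the model is described by its clustering: "including three levels: (1) repeated measures, (2) clustered within the individual, and (3) clustered within a hospital or other therapeutic setting". The treatment comparison is described only in general terms: "A priori defined contrasts between the groups will be tested using the R package “multcomp” and the function “glht". The section does not list fixed effects or write out the contrasts. It does not say whether T0 pain is part of the outcome vector, a covariate, or constrained to be equal between arms.

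The section does state when a baseline variable enters the model. T-tests and chi-square tests "will be performed at baseline to check whether the randomization was successful", and then: "If not, variables for which this was not the case will be included as confounders in the main analyses", once a directed acyclic graph has settled the direction of the relationship. A parallel rule applies to variables flagged by the drop-out analysis.

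**The concern.** Baseline pain is already collected from everyone and is likely to be among the best predictors of pain at 12 months. Using it unconditionally costs nothing. The written rule, applied to baseline pain, would usually leave it out as a covariate: under valid randomisation a baseline test at the .05 level flags a given variable about one time in twenty.

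What follows depends on where T0 sits in the model. If T0 is one of the repeated outcomes and each arm has its own T0 mean, the natural test of a change endpoint is the T5-minus-T0 contrast between arms. That subtracts the whole chance difference at T0, although only a fraction rho of it is expected to persist to T5. The over-correction adds variance to the primary comparison, which adjustment or a common T0 mean would remove.

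**Working it through.** **Inputs from the article.** 252 randomised 1:1, so 126 per arm. Drop-out 25%, so 126 × 0.75 = 94.5 per arm at T5. Partial η² = 0.02, alpha .05, power 95%. Five pain measurements (T0, T1, T2, T3, T5).

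**Assumed.** The T0–T5 correlation rho is not given; 0.5 is used, with a range of 0.3 to 0.7. Variances are taken as equal over time and set to 1, and clustering by centre is ignored.

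**1. The plan's own figure.** For the group-by-time interaction in a repeated-measures F test, f² = 0.02/0.98 = 0.0204 and lambda = N × f² × m/(1 − rho). With N = 94, m = 5 and rho = 0.5, lambda = 94 × 0.0204 × 5/0.5 = 19.18 on 4 and 368 degrees of freedom, and power is 95.4%. (N = 92 gives 94.95%, so 94 is the smallest even number that reaches 95%.) Then 94/0.75 = 125.3, rounded up to 126; two countries give 252, an exact match.

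This reads the calculation as one per country. With four measurements, the count if T0 were a covariate, the same route at rho = 0.5 gives 108, then 144, then 288, which does not match. The match therefore suggests that T0 was counted as a repeated outcome and that 0.5 is a sensible working value. It proves neither.

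**2. Complete data.** Per arm, and up to the common factor 1/n:
- change-score contrast: 2(1 − rho)
- baseline-adjusted or constrained contrast: 1 − rho²
- ratio: (1 − rho²)/[2(1 − rho)] = (1 + rho)/2

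At rho = 0.5 the ratio is 0.75, so 25% of the variance is avoidable.

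**3. With the planned drop-out.** Take the simple case in which all drop-outs contribute T0 only. The variance of the arm contrast is then
- separate T0 means: 2[(1 − rho²)/94.5 + (1 − rho)²/126]
- common T0 mean: 2(1 − rho²)/94.5

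At rho = 0.5: 2(0.75/94.5 + 0.25/126) = 0.01984 (SE 0.141 SD), against 2 × 0.75/94.5 = 0.01587 (SE 0.126 SD). The ratio is 0.80, so 20% is avoidable. If drop-out is instead spread evenly over the follow-up visits, under compound symmetry, the variances are 0.01932 and 0.01535, a cut of 20.5%.

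**4. Range of avoidable variance.**

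| rho | complete data | 25% drop-out, spread evenly | 25% drop-out, T0 only |
|---|---|---|---|
| 0.3 | 35% | 29% | 29% |
| 0.4 | 30% | 25% | 24% |
| 0.5 | 25% | 20% | 20% |
| 0.6 | 20% | 16% | 16% |
| 0.7 | 15% | 12% | 12% |

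These are variances. At rho = 0.5 the standard error is inflated by about 12% with drop-out (sqrt(1/0.80) = 1.118) and 15% with complete data (sqrt(1/0.75) = 1.155).

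**The case against.** The strongest reply is that nothing in the article says baseline pain is merely another repeated measure, unadjusted and unconstrained. A reader might infer this from the change endpoint and the three-level model, but the fixed effects are simply not given, and an article may leave them to a fuller plan. A change endpoint is also compatible with baseline adjustment, which estimates the same quantity. The Introduction words the primary objective as less pain at 12 months, and if the unwritten contrast is the T5 difference alone, the 2(1 − rho) formula does not apply. All of this stands, and it makes the size of the loss conditional. It does not remove the point, because the section goes beyond silence: it writes a test-dependent rule for bringing baseline variables in and gives no unconditional role to baseline pain.

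Two stronger readings are tempting and should not be drawn.

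- **A power figure.** Converting partial η² = 0.02 into a standardised difference of 2 × sqrt(0.02/0.98) = 0.286 for a single 12-month contrast gives power near 50% unadjusted and 62% adjusted among completers at rho = 0.5. The sample size reproduces as an interaction over five measurements, where that η² does not mean a 0.286 SD difference at T5. These percentages are not the trial's power.
- **Bias from chance imbalance.** The standard error of the T0 arm difference is sqrt(2/126) = 0.126 SD. A non-significant imbalance of 0.2 SD would shift a completers' change contrast by (1 − 0.5) × 0.2 = 0.10 SD. This is real in a single realised trial, but it averages to zero over randomisations and is already in the standard error. It is the (1 − rho)² term of step 3 seen from another side, not an additional harm.

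**Conclusion.** The point holds as a conditional efficiency concern. The article fixes a change-from-baseline endpoint, writes no unconditional adjustment for baseline pain, and makes the entry of baseline variables depend on significance tests plus a diagram. If T0 is modelled with separate arm means, about 20% of the variance of the primary contrast is avoidable at an assumed correlation of 0.5 with the planned drop-out. Over 0.3 to 0.7 it runs from 29% down to 12%. These figures rest on a correlation that the article does not supply, equal variances over time, and a reading of the model that the text supports without stating. The analysis as described is not invalid or biased, and the concern does not show that 252 is the wrong sample size. It is still worth settling, because the better form is essentially free.

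**What to change.** In the Statistical Analysis Plan section, state that the primary 12-month group contrast is adjusted for baseline BPI pain whatever the baseline tests show. Either form will do:

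- keep T0 in the outcome vector and constrain the arms to a common T0 mean (time plus group-by-post-baseline-time, with no group term at T0), which retains the T0 data of drop-outs; or
- model T1, T2, T3 and T5 with baseline BPI and baseline-by-time as fixed effects.

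Use the same form for continuous secondary outcomes measured at T0, with their own visits. Under Primary Outcomes, a short clarification that the change is estimated with adjustment for baseline would align the two sections. If a fuller analysis plan already specifies this, only the article's wording needs aligning.

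The cost is a couple of sentences, written before unblinding. No new data, visits or participants are needed. The estimand is unchanged, because randomisation makes the expected T0 difference zero; the Discussion itself assumes that randomisation balances the groups.

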**Secondary Outcome**						
**Pain-related outcomes** Pain distribution (pain drawing)	X	X				X
Pain interference (BPI) Kinesiophobia (TSK) Fear avoidance beliefs (FABQ)	X	X	X	X		X
**Body composition and anthropometrics** Height (SECA stadiometer)	X					
BMI (kg m^−2^) Weight (Tanita) Body fat and fat free mass (TANITA analyzer) Body fat distribution (WC, HC, WHR) Subcutaneous adipose tissue thickness (ultrasound) Muscle thickness (ultrasound)	X	X				X
**Energy balance related behavior** Dietary intake (3-day food diary)	X	X	X	X		X
Sleep quantity (Fitbit Sense) Sleep quality (PSQI)	X	X				X
	X	X	X	X		X
Rest activity cycles (Fitbit Sense) Continuous physical activity (Fitbit Sense)	X	X				X
**Costs** Medical consumption (iMCQ) Indirect health costs (iPCQ)	X	X	X	X	X	X
**Quality of life** Quality of life (EQ-5D-5L)	X	X	X	X	X	X

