**Primary Outcome**			
Pain intensity		Brief Pain Inventory-short form (BPI)	Assessed with 1 question of the BPI: “Please rate your pain by crossing the number that best describes your pain of the last 24 hours on the AVERAGE (0-10).”^42^ The BPI is assessed using the REDCap software.

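### Low-cost improvement: the one-item pain outcome is left out of the 9-month online questionnaire round, so participants lost between 9 and 12 months have no pain score later than month 6

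*Protocol article*

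**What the plan says.** Table 3 describes pain intensity as "Assessed with 1 question of the BPI". The section Primary Outcomes states "The BPI will be collected online using REDCap at baseline (T0" and goes on to list T1 "and at 3-months (T2), 6-months (T3), and 12-months (T5) follow-up". The "Pain intensity (BPI" row of Table 2 marks the same five occasions and leaves T4 blank. The endpoint is fixed at T5: "The primary endpoint is the between-group change in pain intensity from baseline to 12 months follow-up".

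T4 is nevertheless a planned contact. The section Intervention says "Every 3 months, participants will receive and email invitation to complete the follow-up questionnaires via REDCap software", and the footnote to Table 2 reads "T4 = 9 month follow-up (online), T5 = 12 month follow-up (onsite". Table 2 marks three instruments at T4: the medical consumption questionnaire, the productivity cost questionnaire and the row "Quality of life (EQ-5D-5L". Pain interference, the TSK, the FABQ, the PSQI and the food diary are also omitted at T4.

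The Statistical Analysis Plan section specifies a three-level mixed model (repeated measures within individual within setting) and presents it as well suited to data with missing values. The Sample Size Calculation section allows for 25% drop-out over the 12 months of follow-up, without saying when it is expected.

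**The concern.** A likelihood-based mixed model can allow for drop-out that depends on pain scores it contains. It cannot fully allow for drop-out that depends on pain that was never recorded. Someone who answers the T4 round and then misses T5 contributes pain only up to T3, although that person was reached three months before the endpoint. The Intervention section permits concomitant care after the post-intervention measurement, so pain may move between months 6 and 12, and may move differently in the two arms.

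Two things are at stake: a little precision in the T5 contrast, and how far the missing-at-random assumption can be believed for losses between T4 and T5.

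**Working it through.** **1. Does the planned sample size rely on a T4 pain score?** The inputs from Sample Size Calculation are partial η² = 0.02, alpha 0.05, 95% power, 25% drop-out and 1:1 allocation. Correlation 0.5 and sphericity are my assumptions.

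- f² = 0.02/0.98 = 0.0204.
- I used the within-between interaction of a repeated-measures F test with 2 groups, m = 5 occasions and λ = f²·N·m/(1 − 0.5).
- Power is 0.9495 at N = 92 and 0.954 at N = 94, so N = 94.
- 94/0.75 = 125.3, rounded up to 126 per country, and 2 × 126 = 252.

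The plan's figure is matched with the five pain occasions now scheduled. It does not depend on T4.

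**2. Who would add information?** Only people who answer T4 and then miss T5 matter materially.

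- Total loss is 0.25 × 252 = 63.
- If it is even over the five intervals between visits, 63/5 ≈ 13 people are lost between T4 and T5.
- The ceiling is 63, if everyone lost leaves after T4.

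**3. How much better would T5 be predicted?** This is the share of T5 variance explained by earlier pain.

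- Equal correlation ρ = 0.5, with k earlier scores: R² = kρ²/(1 + (k − 1)ρ). For T0-T3 this is 4 × 0.25/2.5 = 0.400. With T4 it is 5 × 0.25/3 = 0.417.
- Correlation fading as 0.7 per visit: from T3, (0.7²)² = 0.24. From T4, 0.7² = 0.49.

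T4 adds almost nothing in the first case and a good deal in the second.

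**4. Variance of the T5 contrast.** I used a large-sample repeated-measures model with a common baseline mean and free visit means by arm. The information is I = Σ ½·π_k·X_k′Σ_k⁻¹X_k, summed over arms and drop-out patterns k, and Var = c′I⁻¹c. Drop-out is monotone and totals 25%. The table shows by how much the variance without T4 exceeds the variance with T4. Correlations and timing are assumed, since the protocol gives neither.

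| Correlation between visits | Even loss | Half of loss after T4 | All loss after T4 (extreme) |
|---|---|---|---|
| Equal, 0.3 to 0.7 | 0.11-0.16% | 0.24-0.37% | 0.43-0.66% |
| Mixture of constant and fading | 0.7% | 1.6-1.7% | 2.9-3.1% |
| Fading, 0.7 or 0.85 per visit | 1.7% | about 4% | about 7% |

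With T4 added, the standard error falls by 0.05-0.8% with even loss (worth 0.3 to 4 of 252 participants), by 0.1-1.9% if half the loss follows T4 (0.6 to 10 participants), and by at most 3.5% in the extreme column. A power of 0.95 becomes 0.950-0.953 with even loss and at most 0.962 in the extreme case.

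**5. Bias when drop-out depends on T4 pain in one arm only.** To first order, bias in that arm's T5 mean = (share of those reaching T4 who are then lost) × β × δ. Here β is the coefficient of T5 on T4 given earlier pain. δ is how much worse T4 pain is in those lost than in those retained, given earlier pain.

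- With even loss the share is 5/80 = 0.0625. I take δ = 0.5 SD for illustration.
- Equal correlation 0.5: β = 0.5/3 = 0.167, so bias = 0.0625 × 0.167 × 0.5 = 0.005 SD.
- Fading 0.7: β = 0.7, so bias = 0.0625 × 0.7 × 0.5 = 0.02 SD.

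The design effect is 2f = 2 × √0.0204 = 0.29 SD. The bias rises in proportion to the share and to δ. If drop-out depends on pain only through the recorded scores, including T4, the T4 item removes it.

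**The case against.** The strongest case against is that nothing here is wrong. The text and Table 2 agree. The chosen pain visits are tied to short-, mid- and long-term effects, and T4 reads as a deliberately reduced round serving the health economic evaluation. All of that stands: this is a design choice that could be improved cheaply.

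A reader might infer that losses will cluster at T5 because it is the only on-site visit in follow-up. The documents do not support this. The pain item is completed online at T5 too, so missing the visit need not mean missing the score. Automated reminders, assessor contact, and a payment made only after the last assessment all favour completion at T5. The columns with late loss are therefore scenarios, not expectations.

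A reader might also infer that information on everyone lost before T5 is thrown away. It is not collected rather than thrown away, and anyone lost before T4 would have given no T4 score. Nor is drop-out related to 9-month pain wholly beyond the model: pain up to T3 is in it, and the T4 EQ-5D-5L could serve as auxiliary information.

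Finally, the three levels described, read as random intercepts, imply equal correlations. This points to the first row of the table. That is fair, and it is why that row comes first. The model's structure does not, however, establish how pain scores are in fact correlated over time.

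**Conclusion.** The point holds as a minor, optional improvement. Under equal correlations, the structure closest to the model described, leaving pain out at T4 raises the variance of the T5 contrast by about 0.1 to 0.4% for even loss up to half of the loss after T4. Across correlation structures the increase is 0.1 to 1.7% with even loss and up to about 4% if half of the 25% loss falls after T4. Power and the planned 252 are essentially unaffected.

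The better argument is credibility. For roughly 13 participants with even loss, a 9-month score would replace a 6-month score as the last pain value before the endpoint. In the illustration it would remove a bias of about 0.005 to 0.02 SD. All these sizes rest on assumed correlations, drop-out timing and drop-out mechanism.

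**What to change.** Add the BPI average-pain item to the existing T4 REDCap form, mark T4 in the pain intensity row of Table 2, and add it to the list of occasions in Primary Outcomes. Include T4 as a visit in the mixed model. T5 remains the primary endpoint, and no test at T4 is needed. If the sponsor prefers the present schedule, one sentence saying why pain is omitted at T4 would close the point.

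The burden on participants is one extra question. The administrative cost is a mid-trial protocol amendment with the ethics committees and a registry update. With 79 participants included at the time of writing, at least 252 − 79 = 173 could still supply a T4 score. Those already past T4 would lack it. Their gap is set by calendar time and not by pain, and the mixed model tolerates it, but the gains above shrink accordingly.
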